
#### Feasibility and acceptability

QbTest opinion questionnaire and interview: Clinician and patient opinion of the QbTest will be assessed via a questionnaire, developed by [name] and currently used to assess QbTest opinion in on-going studies at the Queens Medical Centre, Nottingham. This will provide information on the acceptability of QbTest in routine NHS settings. A subsample (n=20) of families and clinicians will be invited to participate in qualitative interviews to further explore acceptability and feasibility of the QbTest. The subsample will be chosen at random from each participating site, using a random number generator.

Table 1 displays a summary of measures, the informant and the time point of completion. All measures will have a 1-month window for completion, with the exception of the clinic pro-forma which must be completed during or just after the clinic appointment and the QbTest which must form part of the diagnostic or medication assessment. The collected outcome measures for participants who drop out the trial before 6 months will be included in analysis, no further outcome measures will be collected from these participants after they terminate their participation.

**Table 1 BMJOPEN2014006838TB1:** Synoptic table of study measures

[figure not shown]

*If ADHD diagnosis record and medicated within 3 months of baseline assessment (in place of corresponding 3 month assessment in grey).

†Completed at every appointment.

C, clinician completed; P, parent/carer completed; T, teacher completed.

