#### Primary outcome

The primary outcome is the number of consultations until a confirmed clinical diagnosis is reached, as recorded on a short pro-forma. The pro-forma will be completed by clinicians after each consultation with the young person and/or family and documents information about appointment duration, diagnosis and medication/treatment. The pro-forma can be provided by contacting the corresponding author.

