### Sample size and justification

The sample size calculation was based on an audit study data from the Department of Community Pediatrics at the Medway NHS Trust ([name], 2013, unpublished data). Calculations based on this audit study data showed that the mean number of visits needed to achieve an ADHD diagnosis before introduction of the QbTest (control rate) for children aged 6–14 year olds was 2.94 visits and following the introduction of QbTest a diagnosis was reached in a mean of 2.18 visits. Following consultation with stakeholders, it was agreed that this difference (2.94–2.18) represented the minimum clinically important difference, with any smaller difference in mean clinic visits being of debatable value. Therefore, 71 patients in each study group will be required to detect a mean count difference of the above magnitude with 80% power at two tailed 0.05 significance level^36^
^37^ assuming the number of visits follows a Poisson distribution.

Given the evidence that the intraclass correlation coefficients of mental health measures across General Practitioner (GP) centres is extremely low,^38–40^ and results from the Medway audit data indicate that the number of visits needed to achieve an ADHD diagnosis was homogeneous across centres, we will assume that centre effects will not influence the sample size calculation for this study. After taking into account a 20% attrition rate, the final total sample size will be 178. The same calculation performed with 90% power would require a total sample of 234 participants. We aim to recruit 178 participants as a minimum and 234 participants as a maximum. Software Stata V.13 was used for power analysis.

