### Data analysis plan

The analysis will be conducted on an intention-to-treat (ITT) basis. Exploratory analysis will be conducted first for outcome and patient background variables; descriptive statistics of each variable will be presented separately for each group at each follow-up point, with means and SD for normally distributed variables, medians (IQR) for skewed variables and frequency (percentage) for categorical variables. Missing values will be checked and reported. Multiple imputation will be used to hand missing values, based on a multilevel modelling approach.

To compare the number of visits needed to achieve an ADHD diagnosis (either confirmed or excluded) between groups, Poisson regression with binary group status as the explanatory variable will be implemented. To compare clinician's confidence in their diagnostic decisions, multilevel modelling with patient as a level 2 unit will be used to take into account the non-independence within patient data due to repeated measures.^41^

κ Statistics will be used to reflect the stability of diagnosis between first confirmed diagnosis and diagnosis rerated at 6-month follow-up time. κ Statistics will be reported for each group and the stability of diagnosis will be compared between arms using logistic regression. The same analysis approach will be implemented to explore the stability of diagnosis confidence between time of first confirmed diagnosis and 6-month follow-up. To assess the diagnosis accuracy, the sensitivity, specificity, likelihood ratio (LR) ve+, LR ve−, positive predictive value (PPV) and negative predictive value (NPV) will be reported for each group and the test performance will be compared between QbO and QbB arms.^42^
^43^ Receiver operating characteristic curve analyses will be used to obtain the best predictive model based on QbTest scores that discriminates between ADHD ‘positive’ and ADHD ‘negative’ gold standard DAWBA diagnoses.

For treatment related outcomes (phase 2) outcome measures such as SNAP-IV, side effects scale, SDQ and C-GAS scores, multilevel modelling with patient as a level 2 unit will be again applied to quantify the difference between QbO and QbB arms.

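### The dropout rule also ends collection of the clinician-completed visit count, so families who leave the research before diagnosis have a truncated or missing primary outcome

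*Protocol article*

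**What the plan says.** All references are to the Protocol article.

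- **Primary outcome** defines the endpoint and its source: "The primary outcome is the number of consultations until a confirmed clinical diagnosis is reached, as recorded on a short pro-forma". The clinic supplies it: "The pro-forma will be completed by clinicians after each consultation with the young person and/or family".
- **Feasibility and acceptability** (text introducing Table 1) keeps what was gathered before a participant leaves: "The collected outcome measures for participants who drop out the trial before 6 months will be included in analysis". It then closes collection: "no further outcome measures will be collected from these participants after they terminate their participation". The same paragraph names the pro-forma when it sets the one-month completion window, "with the exception of the clinic pro-forma which must be completed during or just after the clinic appointment". So the pro-forma is counted among the measures and is exempted from the window, but not from the dropout rule.
- **Data analysis plan** states: "The analysis will be conducted on an intention-to-treat (ITT) basis". For gaps it states: "Multiple imputation will be used to hand missing values, based on a multilevel modelling approach".
- **Sample size and justification** applies attrition to a calculation based on the visit count: "After taking into account a 20% attrition rate, the final total sample size will be 178".

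**The concern.** The trial gathers two kinds of data. Questionnaires and the second QbTest need effort from the family or the school. The visit count needs only that the child keeps attending a diagnostic assessment that is usual care, and that the clinician fills in a short form. The dropout rule does not separate the two. When a family terminates participation before a diagnosis is confirmed or excluded, the count stops part-way even if the appointments go on.

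The primary comparison is presented as intention-to-treat. A count that stops early is not the participant's outcome. Entered as it stands, it understates the number of visits; set to missing, it must be imputed. Both are harmless only under assumptions about why families leave. Two reasons for leaving would matter: a long assessment gives more time in which to leave, and only QbOpen families see a report before 6 months. The article has no data on either, so this is a risk and not a demonstrated bias. What makes the point worth raising is that the missing information would often exist in the clinic.

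**Working it through.** **Inputs** (Sample size and justification; Randomisation and blinding): means 2.94 and 2.18 visits, difference 0.76; Poisson counts; two-sided 0.05; 80% power; 71 per arm; 20% attrition; total 178; equal allocation.

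**1. Reproduce the plan's figure.** On the log rate ratio:

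n per arm = (z₀.₉₇₅ + z₀.₈₀)² × (1/2.94 + 1/2.18) / [ln(2.94/2.18)]² = 7.849 × 0.7989 / 0.2991² = 70.1, rounded up to 71.

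Attrition: 142 / 0.8 = 177.5, rounded up to 178. Both stated figures reproduce. The 90% power option gives 93 or 94 per arm depending on the formula, and a total of 233 to 236 against the stated 234. The sample size arithmetic is not in question.

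**2. How many primary outcomes the rule can affect.** The planned attrition is 0.20 × 178 = 35.6, about 36 participants. Only those who leave before diagnosis have an incomplete count. Their share of all leavers, f, is not in the article, so it is an assumption shown as a range. The number affected is 0.20 × f × 178, and the number with complete counts per arm is (178 − affected)/2.

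**3. Power.** Power = Φ(0.2991/SE − 1.96), with SE = √(0.7989/n). At n = 71, SE = 0.1061 and power is 80.5%. Taking all incomplete counts as lost:

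| f (assumed) | Affected, of 178 | Complete counts per arm | Power |
|---|---|---|---|
| 0% | 0 | 89.0 | 88.4% |
| 25% | 9 | 84.6 | 86.8% |
| 50% | 18 | 80.1 | 85.0% |
| 75% | 27 | 75.7 | 82.9% |
| 100% | 36 | 71.2 | 80.6% |

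A difference-of-means formula gives values within 0.3 percentage points of these (80.9% to 88.7%). The top row is the ceiling, reached if no count is lost. The worst row still meets the stated 80%.

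**4. Sensitivity to selective leaving (illustration only).** If a fraction p of one arm has no usable count, and those participants would have needed g more or fewer visits than the rest, an analysis that does not correct for this misstates that arm's mean by p × g. With g = 1 visit, assumed and in one arm only:

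- p = 0.05 (f = 25%): 0.05 visits, or 0.05/0.76 = 7% of the target difference.
- p = 0.20 (f = 100%): 0.20 visits, or 0.20/0.76 = 26% of the target difference.

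Neither g nor its restriction to one arm comes from the article. Imputation could remove some of the shift if its assumptions held.

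**The case against.** Several parts of the case against stand.

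- **Skipping questionnaires is not clearly termination.** The rule covers those who drop out and terminate participation. A family that stops returning forms could be treated as still enrolled with missing items, and its pro-forma would continue. A reader might infer that questionnaire fatigue automatically forfeits the primary outcome; the article does not say so. It also does not say where the line falls.
- **Not every leaver is affected.** The count ends at diagnosis, and data gathered before leaving are analysed. A reader might infer that the whole 20% is lost; that is an upper end.
- **Some loss cannot be recovered.** The 20% is a planning allowance that is not split by cause. Where the child stops attending, or the family refuses use of its data, no withdrawal rule completes the count.
- **Power is not short.** A reader might infer an underpowered trial from the range in the working. The inflation already covers the loss, so the higher values would be a bonus.
- **Days to diagnosis is not simply lost.** It is analysed by Kaplan-Meier and log-rank methods, which use follow-up to the point of censoring, although censoring linked to prognosis would remain a concern.
- **Levels of withdrawal may be set out in the full protocol or the consent forms**, which are not shown. This would answer a complaint that the topic is missing. It does not answer this point, because the article states a rule, and the rule as stated covers the pro-forma.

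**Conclusion.** The point holds in a limited form. As written, the rule ends collection of the pro-forma along with everything else, so participants who leave before diagnosis but remain in clinic have a truncated or missing primary outcome in an analysis described as intention-to-treat. Those who leave after diagnosis are unaffected for the primary count.

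On the assumption that 25% to 100% of the planned leavers go before diagnosis, about 9 to 36 of 178 counts (5% to 20%) are affected, and an unknown part of these is recoverable. The 20% is itself a planning figure.

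A reader might go further and conclude that the primary result will be biased between arms. The article does not support that: it contains nothing on why families leave or whether leaving differs by arm, and the 26% figure is an illustration on assumed values. The case for change is that a small amendment would remove much of the reliance on an untested missing-data assumption for the primary outcome.

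**What to change.** Replace the closing sentence on dropouts in Feasibility and acceptability with a graded rule:

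1. Participants who wish to stop research questionnaires or the second QbTest are asked whether the clinician pro-forma (visits, dates, diagnosis) and the 6-month clinician re-rating may still be collected.
2. Collection of these ends only if the family refuses.
3. The level of withdrawal and its date are recorded, so that partial withdrawal, refusal of data use and clinic non-attendance can be told apart in the analysis.
4. While the pro-forma is still being collected for a QbBlind participant, the report stays withheld under the existing 6-month rule in Trial design. Otherwise release at withdrawal would alter the later counts.

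**Cost.** An ethics amendment and revised information and withdrawal wording. Recruitment has already started and nine Trusts are listed, so the new wording must reach active sites. Families already enrolled consented on the existing terms and would be asked for agreement at the time of withdrawal. No research visit or family task is added; clinicians continue the short form they already complete.

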### Sample size and justification

The sample size calculation was based on an audit study data from the Department of Community Pediatrics at the Medway NHS Trust ([name], 2013, unpublished data). Calculations based on this audit study data showed that the mean number of visits needed to achieve an ADHD diagnosis before introduction of the QbTest (control rate) for children aged 6–14 year olds was 2.94 visits and following the introduction of QbTest a diagnosis was reached in a mean of 2.18 visits. Following consultation with stakeholders, it was agreed that this difference (2.94–2.18) represented the minimum clinically important difference, with any smaller difference in mean clinic visits being of debatable value. Therefore, 71 patients in each study group will be required to detect a mean count difference of the above magnitude with 80% power at two tailed 0.05 significance level^36^
^37^ assuming the number of visits follows a Poisson distribution.

Given the evidence that the intraclass correlation coefficients of mental health measures across General Practitioner (GP) centres is extremely low,^38–40^ and results from the Medway audit data indicate that the number of visits needed to achieve an ADHD diagnosis was homogeneous across centres, we will assume that centre effects will not influence the sample size calculation for this study. After taking into account a 20% attrition rate, the final total sample size will be 178. The same calculation performed with 90% power would require a total sample of 234 participants. We aim to recruit 178 participants as a minimum and 234 participants as a maximum. Software Stata V.13 was used for power analysis.

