## Study limitations

The diagnosis and management of ADHD is inconsistent, as such the ‘assessment as usual’ practice will vary across sites. In order to document this difference each site completed a questionnaire prior to their participation in the trial detailing their ‘assessment as usual’ procedure. Furthermore, basic descriptions of ‘assessment as usual’ will be recorded in the pro-forma (such as number and length of appointments, decision-making and medication). Given this is a pragmatic trial conducted in real-world settings we are interested in the impact of adding QbTest feedback to ‘assessment as usual’—without changing other aspects of practice. In order to minimise the trial results being influenced by practice in any one site, we are recruiting participants across multiple sites in different regions of the country and include both CAMHS and community paediatrics. In our design, we have attempted to control for variations between sites by stratification of randomisation by site.

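### The sample size and primary test assume Poisson variance for a count that cannot be below 1, so the 5% error rate and 80% power are calibrated only if the within-site variance equals the mean

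*Protocol article*

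**What the plan says.** Under *Primary outcome*: "The primary outcome is the number of consultations until a confirmed clinical diagnosis is reached, as recorded on a short pro-forma". The same section adds: "The pro-forma will be completed by clinicians after each consultation with the young person and/or family". The consultation at which the diagnosis is made is itself counted, so the smallest possible value is 1.

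*Sample size and justification* takes its planning means from the Medway audit. Before QbTest the mean "for children aged 6–14 year olds was 2.94 visits"; afterwards, "following the introduction of QbTest a diagnosis was reached in a mean of 2.18 visits". From these it derives 71 per group "with 80% power at two tailed 0.05 significance level", "assuming the number of visits follows a Poisson distribution". Allowing for 20% attrition, the minimum total is 178; the maximum of 234 corresponds to 90% power. No standard deviation or variance of visits is given.

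For the primary comparison, *Data analysis plan* states: "Poisson regression with binary group status as the explanatory variable will be implemented". It names no dispersion parameter, robust standard error or site term for this model. *Randomisation and blinding* stratifies allocation by site.

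**The concern.** A Poisson model ties the variance to the mean. In ordinary Poisson regression the standard error comes from that tie, not from the observed scatter. If the true variance is smaller, the confidence interval is too wide and power is wasted. If it is larger, the interval is too narrow and the false-positive rate exceeds 5%.

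Two features of this outcome make equality a coincidence. The count starts at 1, which lowers the variance relative to a Poisson count with the same mean. Patients and clinicians differ within a site, which raises it. The primary p-value, its confidence interval and the stated power all depend on where the balance falls, and the article gives no figure from which to judge.

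**Working it through.** **Inputs.** From *Sample size and justification*: means 2.94 and 2.18 (difference 0.76), two-sided 5%, 80% power, 71 per group, 20% attrition. Equal allocation is from *Randomisation and blinding*. The ratio φ = variance/mean is not in the document and is assumed over a range.

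**1. The plan's figure reproduces.** On the log rate-ratio scale, n = (1.960 + 0.842)² × (1/2.94 + 1/2.18) / [ln(2.94/2.18)]² = 70.1, rounded up to 71. Then 142/0.8 = 177.5, giving 178. The arithmetic is right under variance = mean.

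**2. The assumption cannot hold literally.** A Poisson count would put exp(−2.94) = 5.3% and exp(−2.18) = 11.3% of patients at zero visits, which is impossible here.

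**3. Effect of φ at 71 per group.** The Poisson standard error of the difference is SE = √((2.94 + 2.18)/71) = 0.2685. With the same φ in both arms and Φ the standard normal distribution function:

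- type I error of the plain Poisson test = 2[1 − Φ(1.96/√φ)]
- its power = Φ((0.76/SE − 1.96)/√φ)
- power with a valid standard error = Φ(0.76/(SE√φ) − 1.96)
- n per group for 80% power with a valid standard error = 69.6φ

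| φ (assumed) | Type I, plain Poisson | Power, plain Poisson | Power, valid SE | n per group (total with attrition) |
|---|---|---|---|---|
| 0.6 | 1.1% | 87% | 95% | 42 (105) |
| 0.75 | 2.4% | 84% | 90% | 53 (133) |
| 1.0 | 5.0% | 81% | 81% | 70 (175) |
| 1.25 | 8.0% | 78% | 72% | 87 (218) |
| 1.5 | 11% | 76% | 64% | 105 (263) |
| 2.0 | 17% | 73% | 52% | 140 (350) |

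The φ = 1 row uses the difference-of-means formula, which gives 70; the log-scale formula in step 1 gives 71.

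**4. Distributions that respect the floor.** For 1 + Poisson the variance is the mean minus 1, so φ is 1.94/2.94 = 0.66 and 1.18/2.18 = 0.54. For a zero-truncated Poisson, φ is 0.81 and 0.65. For a geometric count starting at 1 (constant chance of diagnosis at each visit), φ = mean − 1, so 1.94 and 1.18. Simulation at 71 per group gave:

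| Distribution of visits | Type I, plain | Power, plain | Power, robust SE |
|---|---|---|---|
| Poisson | 4.9% | 81% | 81% |
| 1 + Poisson | 1.4–1.7% over repeated simulations | 87% | 95–96% |
| Zero-truncated Poisson | 3.0% | 85% | 91% |
| Shifted negative binomial, φ = 1 | 5.0% | 81% | 80% |
| Shifted negative binomial, φ = 1.5 | 11% | 77% | 64% |
| Geometric from 1 | 16% | 75% | 64% |

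Robust type I error was 5.2–5.7% throughout. The φ = 1 row shows that a count starting at 1 can still be calibrated, but only because its variance happens to match its mean.

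**5. Site variation.** With allocation balanced within site, differences between sites cancel from the arm comparison, so the relevant variance is the average within-site variance. If visits are Poisson within each site, that average equals the overall mean and the plain standard error is right. Simulation with 9 sites, 142 participants and no treatment effect agrees. With overall φ about 1.57, plain Poisson type I error was 4.8% under stratified allocation, against 12.3% unstratified. With φ about 2.05 it was 4.9% against 15.8%. Unadjusted robust errors in this setting gave only 1–2%, because they count between-site variance that stratification has removed.

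**The case against.** - **The one departure that the document establishes is harmless for type I error.** The floor at 1 lowers the variance, so error stays below 5% and power above 80%. This stands. The cost in that direction is lost efficiency: 87% power where 95% was available.
- **The harmful scenarios rest on ratios that appear nowhere in the document.** This also stands. A ratio of 2 in both arms exceeds even the geometric case (1.94 and 1.18). The figures at 1.5 and 2 illustrate sensitivity and do not predict the trial's result.
- **Site variation as the cause.** A reader might infer inflated error from the statement in *Study limitations* that usual assessment "practice will vary across sites". The document does not support that inference: randomisation is stratified by site, and step 5 shows that type I error then stays near 5%. The sample size section also reports that the audit found visits homogeneous across centres. Only patient or clinician variation within a site could inflate the error, and the document does not quantify it.
- **A statistical analysis plan may specify a robust error.** It may, and the article does not say how the standard error is obtained. But the article itself names the distribution, sizes the trial on it and names the model. A later choice of standard error would not free the stated power from the assumption.
- **Recruitment may reach 234.** That is about 94 evaluable per group (234 × 0.8 / 2 = 93.6), which keeps 80% power with a valid error up to a ratio of about 94/69.6 = 1.35. The committed minimum remains 178.

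**Conclusion.** The point holds as one of calibration. The sample size and the named primary model both fix variance = mean for a count that cannot follow a Poisson distribution. The nominal 5% and stated 80% are both met only if the within-site variance equals the mean. On the floor alone (1 + Poisson), type I error is about 1.5% and power 87% instead of 95%. If within-site variation took the variance to 1.5 times the mean, type I error would be about 11%, and a valid test would have 64% power.

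These sizes assume 71 evaluable patients per group, the audit means, and the stated distribution or ratio. A reader might conclude that the trial is underpowered or that its false-positive rate is inflated. The document supports neither conclusion: it gives no variance, and the only departure that it establishes is conservative. There is no arithmetic error in the 71 or the 178.

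**What to change.** Fit the Poisson model with group and the stratification factor (site), using robust (sandwich) or quasi-Poisson standard errors. Site should be in the model: a robust error without it counts between-site variance that stratification has removed, and can be markedly conservative.

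Take the variance of visits from the Medway audit that supplied the means, separately before and after QbTest, and within centre where the audit allows. Restate the power of 71 per group as conditional on that variance, with a range of variance-to-mean ratios such as the one tabulated above.

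The cost is one line of analysis wording and one recalculation from the audit. The stated power may move either way. Nothing changes in recruitment procedures, data collection or care.
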